## Abstract

**Background:**

Tibial shaft fractures (TSFs) are among the most common long bone injuries often resulting from high-energy trauma. To date, musculoskeletal complications such as fracture-related infection (FRI) and compromised fracture healing following fracture fixation of these injuries are still prevalent. The relatively high complication rates prove that, despite advances in modern fracture care, the management of TSFs remains a challenge even in the hands of experienced surgeons. Therefore, the Fracture-Related Outcome Study for operatively treated Tibia shaft fractures (F.R.O.S.T.) aims at creating a registry that enables data mining to gather detailed information to support future clinical decision-making regarding the management of TSF’s.

**Methods:**

This prospective, international, multicenter, observational registry for TSFs was recently developed. Recruitment started in 2019 and is planned to take 36 months, seeking to enroll a minimum of 1000 patients. The study protocol does not influence the clinical decision-making procedure, implant choice, or surgical/imaging techniques; these are being performed as per local hospital standard of care. Data collected in this registry include injury specifics, treatment details, clinical outcomes (e.g., FRI), patient-reported outcomes, and procedure- or implant-related adverse events. The minimum follow up is 12 months.

**Discussion:**

Although over the past decades, multiple high-quality studies have addressed individual research questions related to the outcome of TSFs, knowledge gaps remain. The scarcity of data calls for an international high-quality, population-based registry. Creating such a database could optimize strategies intended to prevent severe musculoskeletal complications. The main purpose of the F.R.O.S.T registry is to evaluate the association between different treatment strategies and patient outcomes. It will address not only operative techniques and implant materials but also perioperative preventive measures. For the first time, data concerning systemic perioperative antibiotic prophylaxis, the influence of local antimicrobials, and timing of soft-tissue coverage will be collected at an international level and correlated with standardized outcome measures in a large prospective, multicenter, observational registry for global accessibility.

**Trial registration:**

ClinicalTrials.gov: NCT03598530.

**Supplementary Information:**

The online version contains supplementary material available at 10.1186/s12891-020-03930-x.

## Background

Tibial shaft fractures (TSFs) are among the most common long bone injuries [1]. Their incidence has been reported on several occasions and varies between 8.1 and 37.0 per 100,000 persons/year, with a decrease over recent years [1–3]. Over 15% of tibia fractures are classified as open, representing the most common open long bone fracture [4, 5]. This is one of the reasons why musculoskeletal complications such as fracture-related infection (FRI) and compromised fracture healing remain prevalent with these types of injuries. Currently, the incidence of FRI ranges from 1%, following operative fixation of closed low-energy fractures [6], to 25–30% in complex open tibia fractures [5]. Nonunion rates vary from 3 to 17% [7–9]. Furthermore, annual reoperation rates following the operative treatment of TSFs have been reported to vary between 12 and 44% [10]. These high complication rates suggest that despite advances in modern fracture care, treatment of TSFs poses a challenge even for experienced surgeons.

Although several high-quality studies have already addressed individual research questions, knowledge gaps remain. Hence, the aim of the Fracture-Related Outcome Study for operatively treated Tibia shaft fractures (F.R.O.S.T.) is to create a registry that allows data mining to gather information that will assist in future clinical decision-making.

## Methods/design

### Study objectives

The registry’s main objective is to collect data on the operative treatment and outcome of TSFs in patients aged ≥18 years in an international and multicenter setting.

Specifically, this registry aims to:
Increase knowledge and evidence with respect to the epidemiology and treatment concepts of TSFs worldwide by collecting prospective data in a structured and systematic manner.Identify risk factors (e.g., injury, patient, or treatment) for favorable and unfavorable outcomes and complications.Allow data mining to gather evidence to optimize the clinical decision-making process, particularly to (i) develop strategies that intend to prevent musculoskeletal complications and (ii) generate hypotheses for future studies.

### Study design

This is a prospective, international, multicenter, observational registry. Patient treatment is being performed according to the local standard of care (routine), that is, the study protocol (supplementary material) does not influence the clinical decision-making procedure or materials or surgical/imaging techniques. The sites that are currently included are summarized in Table 1.

**Table 1 Tab1:** Sites currently included in the Fracture-Related Outcome Study for operatively treated Tibia shaft fractures (F.R.O.S.T.)

**Department of Trauma Surgery, University Hospitals Leuven, Leuven, Belgium**	**PI (PCI):** [name]
**Department of Trauma-, Hand- and Reconstructive Surgery, University Hospital Muenster, Muenster, Germany**	**PI (Co-PCI):** [name]
**Department of Trauma Surgery, Erasmus MC, University Medical Center Rotterdam, Rotterdam, The Netherlands**	**PI (Co-PCI):** [name]
**Department of Orthopaedic and Trauma Surgery, University Hospital Basel, Basel, Switzerland**	**PI** [name]
**Division of Orthopaedics, Faculty of Medicine and Health Sciences, Stellenbosch University, Tygerberg Hospital, Cape Town, South Africa**	**PI** [name]
**Department of General Trauma and Reconstructive Surgery, University Hospital, LMU Munich, Munich, Germany**	**PI** [name]
**Department of Orthopaedic Surgery and Rehabilitation, Vanderbilt University Medical Center, Nashville, TN, United States of America**	**PI** [name]
**Department of Orthopedic Surgery, NYU Langone Orthopedic Hospital, New York, NY, United States of America**	**PI** [name]
**Department of Orthopaedic Surgery, NYU Langone Orthopedic Hospital and Jamaica Hospital Medical Center, New York, NY, United States of America**	**PI** [name]
**Department of Orthopaedic Surgery, Korea University College of Medicine, Guro Hospital, Guro-gu, Seoul, Republic of Korea**	**PI** [name]
**Department of Orthopaedic Surgery, Sengkang General Hospital, Singapore**	**PI** [name]
**Department of Trauma, UniversitätsSpital Zürich, University of Zurich, Zurich, Switzerland**	**PI** [name]
**Academic Department of Trauma and Orthopaedics, School of Medicine, University of Leeds, Leeds General Infirmary, Leeds, United Kingdom** ***(Planned New Site)***	**PI** [name]
**Department of Orthopaedics and Traumatology, University Medical Center, Johannes Gutenberg-University, Mainz, Germany** ***(Planned New Site)***	**PI** [name]
**Department of Orthopaedics and Traumatology, Queen Mary Hospital, University of Hong Kong, Pokfulam, Hong Kong** ***(Planned New Site)***	**PI** [name]
**Department of Surgery, Franciscus Gasthuis en Vlietland Hospital, Rotterdam, The Netherlands** ***(Planned New Site)***	**PI** [name]
**Department of Orthopedics, Elisabeth-TweeSteden Hospital, Tilburg, Netherlands** ***(Planned New Site)***	**PI** [name]

Site selection was based on a world-wide open call by the AO Foundation. It was decided that sites should be included from different parts of the world. The following criteria were developed during the decision-making process:

1. A site should be able to recruit a minimum number of patients within the planned recruitment time (a minimum of 65–75 patients per year).

2. A site should make sure that patients are in follow up for a minimum time of 1 year.

3. Sites must be able to anonymize their clinical data (e.g., radiological images).

4. Sites are able to plan patient visits as per standard of care at the site.

5. Sites should agree to the administrative conditions (reimbursement, contracts) and receive approval from their local ethical committee.

6. Sites should be able to perform registry related documentation

*PCI* Principal Coordinating Investigator, *co-PCI* co-Principal Coordinating Investigator, *PI* local Principal Investigator

### Participants

#### Sample size estimation

Owing to the exploratory nature of this registry, there is no formal sample size calculation. Approximately 1000 tibial shaft fractures are expected to be included in the 3 years enrollment period. A sample size of 1000 will allow the identification of infrequent adverse events (AEs) as well as rare treatment concepts. The following inclusion and exclusion criteria are specified:
Inclusion criteria
Aged ≥18 years at the time of the injury.The diagnosis of a primary TSF, a fracture type 42, according to the Arbeitsgemeinschaft für Osteosynthesefragen (AO)/Orthopaedic Trauma Association (OTA) Fracture and Dislocation Classification (Fig. 1), that will be treated operatively as part of the standard of care.Informed consent will be obtained based on:
The ability of the patient or an assigned representative to understand the content of the patient information/Informed Consent Form (ICF).Signed and dated Institutional Review Board (IRB)/Ethics Committee (EC)-approved written informed consent.Exclusion criteria
Pathological fractures caused by malignancy.Patients participating in any other medical device or medicinal product study within the previous month that could influence the results of the present study.Patients who cannot provide independent written informed consent unless defined, and IRIR/EC-approved procedures for consenting such vulnerable patients are in place.

**Fig. 1 Fig1:**
[figure not shown]
AO/OTA tibial shaft fracture (TSF) classification

### Procedures

#### Recruitment

First, the investigator or another appropriately trained member of the research team at the study site identifies all eligible patients. These patients should meet all inclusion criteria and none of the exclusion criteria. Next, they inquire about the patient’s interest in participating in this study. If the patient wishes to participate, a legally eligible member of the research team goes through the informed consent process with the patient, explaining the study’s purpose, procedures, risk/benefits, alternatives to participation, and data protection. Each patient who chooses to participate signs and dates an ICF*.* All consenting patients are allocated a unique patient trial number. A protocol deviation is documented for patients found ineligible after treatment, indicating which inclusion/exclusion criterion (or criteria) was (or were) violated.

The follow-up (FU) population will consist of patients who have signed informed consent, are eligible (i.e., meet all inclusion and none of the exclusion criteria), and have commenced treatment (i.e., definitive treatment). Recruitment is planned to take 36 months to enroll a minimum of 1000 patients. An evaluation will take place at the end of this period. If deemed necessary, due to a high percentage of dropouts for example, the study period may be extended.

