#### Interventions and study procedures

Patients will undergo fracture fixation using osteosynthesis, including single- or multiple-staged procedures (e.g., initial external fixation with later conversion to internal fixation). The operative treatment for TSFs in adults mainly depends on the fracture characteristics and extent of the soft tissue damage and is to be performed according to the standard (routine) care procedures based on the individual clinician’s judgment and patient characteristics. Neither specific treatment nor specific time points for FU visits are dictated for registry purposes.

Registry-related assessments will include radiographic evaluations, performed by the treating surgeon at the treatment visit and at defined time points after treatment, following each site’s standard (routine) visit schedule for up to 36 months. Radiographic images and/or clinical pictures will be stored to enable future ad-hoc analysis after de-identification. If patients are unable to attend the last planned FU visit, they will be contacted by e-mail or phone to document the final outcomes, especially patient-reported outcomes (PROs) and complications not previously captured. The planned registry schedule is displayed in Table 2 over the 36-months FU visit period.

**Table 2 Tab2:** Registry schedule for the Fracture-Related Outcome Study for operatively treated Tibia shaft fractures (F.R.O.S.T.)

	Baseline	Treatment	Post-treatment visit 1^a^	Post-treatment visit 2^a^	Post-treatment visit 3^a^	Additional Post-treatment visit(s)^a^
	–	Day 0	6 weeks (target 42 days: range 14 to 105)	6 months (target 183 days; range 106 to 260)	12 months (target 365 days, range 261 to 456)	Up to 36 months
Eligibility	X					
Patient information/consent	X^b^					
Demographics	X					
Medical history and pre-treatment values	X					
Injury(s) details	X					
Treatment details		X^c^				
Clinical outcome(s)			X	X	X	X
Patient-reported outcome(s)						
PROMIS: Global Health	X		X	X	X	X
PROMIS: Physical Function	X		X	X	X	X
PROMIS: Pain Interference			X	X	X	X
Pain numeric rating scale (NRS)			X	X	X	X
Complications			X	X	X	X
Images and/or other clinical pictures	X^d^	X^d^	X^d^	X^d^	X^d^	X^d^

^a^ If a patient does not visit at the specified time point, the visits will be assigned according to the specified rules. Additional postoperative visits may take place up to 36 months after day 0

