^b^ Informed consent may occur after treatment under certain circumstances (see details in section 10). No data can be collected in the eCRF prior to consent

^c^ Treatment may occur on the same day as the baseline. Treatment of tibial fractures may require two or more stage-procedures (e.g., external fixation and secondary internal fixation) performed on different days

^d^ Images (X-ray images, CT scans, etc.) and clinical pictures are collected ONLY if they are taken as part of the standard of care (routine) procedures. All images and photographs will be de-identified

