### Outcome measures

The data collected in this registry will include treatment details, clinical outcomes, PROs, and procedure- or implant-related AEs. Documentation of treatment details will comprise information about the time from injury to index surgery, duration of surgery, number of stages of the procedure, skin preparation, tourniquet use, details about debridement and irrigation, type of reduction/fixation method, specifics related to the fixation devices (e.g., material type, implant dimension*)*, intraoperative blood loss, as well as the use of local agents to promote bone healing. Moreover, information relating to the perioperative use of either prophylactic or curative systemic antibiotics and application of local antimicrobials will be documented and entered in the database. Furthermore, information pertaining to soft-tissue management will be recorded, such as timing and details of wound closure, soft-tissue coverage, and flap type. For concomitant fractures of the tibia or fibula, the treatment method will be documented. If further treatments are performed during the index surgery, these will also be captured.

Clinical outcome documentation will include time to bone healing/union, the presence of malalignment, malrotation or malunion, and the time to full weight bearing. Time to bone healing is defined as the time elapsed between definitive treatment and bony union. The healing status assessment will be based on a combination of clinical and radiological parameters, which will be judged by the treating surgeon. Clinically, healing will be rated as complete when the patient is able to walk without support in the absence of pain or tenderness at the fracture site. Radiologically, the modified RUST score [18] will be determined by scoring each cortex on the anteroposterior (AP) and lateral radiographs as 1 = no callus, 2 = callus present, 3 = bridging callus, and 4 = remodeled, fracture not visible. The modified RUST score is the sum of these and therefore has a value from 4 to 16.

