Malalignment, malrotation, and malunion will be determined by the treating surgeon. *Malalignment* will be measured on AP and lateral radiographs using the method described by Freedman et al. [19]. An angulation of > 5° in any plane is regarded as malalignment. *Malrotation* will be measured clinically and/or radiologically, depending on the availability of rotational CT and the local standard of care. A rotational deviation of > 10° is regarded as malrotation [20]. *Malunion* denotes that fracture-healing results in deformity corresponding to one or a combination of the following: > 5° malalignment, > 10° of malrotation, and/or a shortening of > 1 cm [20]. *Time to full weight bearing* is defined as the time elapsed between definitive treatment and the treating surgeon allowing the patient to bear full weight on the injured leg with or without any support. *Global health*, *pain interference*, and *physical function* will be documented using the corresponding domains of the Patient-Reported Outcomes Measurement Information System (PROMIS®) questionnaires. PROMIS® was established in 2004 with funding from the National Institutes of Health (NIH) as one of the NIH Roadmap initiatives for Medical Research and provided standardized and validated measures [21].

The questionnaires are designed to be completed by the patients without assistance. However, we anticipate that some patients may be unable to attend the planned FU visit(s). In these cases, patients will be contacted by e-mail or phone to document the outcome per interview. Interviews have been shown to produce similar scores compared to those obtained after completion of the questionnaires by the patients themselves [22, 23].

Validated translations of PROMIS® are available in an increasing number of languages. For this registry, only sites for which validated language versions are available will be asked to complete the forms. As other translations become available, these will be implemented immediately after notification of the respective IRB/EC.

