The pre-injury status concerning global health and physical function will be captured retrospectively at baseline and entered in the database. The *global health assessment* reflects an individual’s evaluation of their physical, mental, and social health. In this registry, a short form of 10 questions (v1.2) will be used. The *pain interference* questionnaire covers pain interference with physical, social, and recreational activities and will be documented with a short form of 8 questions (v1.0 – Pain Interference 8a). The *physical function (mobility)* questionnaire assesses the patients’ ability to perform various daily living activities, documented in a short form of 10 questions (v2.0 – Physical Function 10b). *Pain* will be documented on a numeric rating scale (NRS) from 0 to 10 for the injured leg, the knee of the injured leg, and the ankle of the injured leg. *Procedure- or implant-related adverse events*, i.e., complications, will only be documented for the injured tibia, but not for concomitant fractures in the fibular, malleolar, or other regions.

In addition to AEs entered via free text, some pre-defined complications will be captured. *Intraoperative pre-defined complications* include iatrogenic fracture, iatrogenic vessel damage, excessive bleeding, iatrogenic nerve damage, and intraoperative resuscitation. *Postoperative pre-defined complications* include compartment syndrome, FRI, nonunion, refracture/peri-implant fracture, secondary loss of reduction, secondary displacement or breakage of the fixation material, deep vein thrombosis, pulmonary embolism, ongoing pain medication, or inability to bear full weight 1 year after definitive treatment.

FRI will be diagnosed as defined in the recently published consensus definition [24] and subsequent update [25]. Additional contextual information will be collected for all AEs and comprises the start date of the event, its severity and seriousness, information about the related additional treatment(s), date of recovery, and the event’s outcome.

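### Follow-up entry and the time outcomes start at definitive treatment, so comparisons by strategy omit the interval between stages and any consented patient who fails before definitive fixation

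*Protocol article*

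**What the plan says.** Under Recruitment, the follow-up population is limited to patients who have consented, are eligible and "have commenced treatment (i.e., definitive treatment".

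Under Outcome measures, three items use the same starting point:
- "Time to bone healing is defined as the time elapsed between definitive treatment and bony union".
- Time to full weight bearing "is defined as the time elapsed between definitive treatment and the treating surgeon allowing the patient to bear full weight".
- The list of postoperative complications includes "inability to bear full weight 1 year after definitive treatment".

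Staged care is part of the registry. Interventions and study procedures gives the example of "initial external fixation with later conversion to internal fixation", and footnote c of Table 2 adds "Treatment of tibial fractures may require two or more stage-procedures", performed on different days.

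The number of stages and the time from injury to index surgery are recorded (Outcome measures). Statistical analyses plans summaries stratified by the treatment received, and takes the total population as the denominator for complication rates without linking it to a named population. The Discussion gives the registry's main purpose as evaluating the association between treatment strategies and outcomes.

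**The concern.** For a single-stage patient, definitive treatment is the first operation. For a patient with temporary external fixation followed by internal fixation, it is a later operation. A rule that looks uniform therefore places the two groups at different points in their course after injury.

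Two things follow when outcomes are set out by strategy. First, days already spent with a stabilised but unhealed fracture are not counted for staged patients, so their healing and weight-bearing times come out shorter. Second, staged patients must reach definitive treatment to be followed at all, and deaths and amputations between stages fall outside the follow-up population. A single-stage patient cannot be lost in this way once surgery has begun.

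Staging is likely to go with severe soft-tissue injury, where early failure matters most. A simple descriptive table of healing time by treatment type would carry the distortion; no formal test is needed for it to mislead.

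**Working it through.** The article states no figure for this point, so there is none to reproduce. The first step compares definitions; the others are illustrations on assumed inputs.

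**Step 1. The definitions side by side**

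| Item | Single-stage patient | Staged patient |
|---|---|---|
| Entry to follow-up population | First operation | Definitive operation, if reached |
| Origin of time to union and to full weight bearing | First operation | Definitive operation |
| One-year weight-bearing item, counted from first operation | One year | One year plus the gap between stages |
| Death or limb loss after first surgery, before definitive treatment | Cannot occur | Outside the follow-up population |

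Every difference runs in favour of staged treatment. Where the external fixator is itself the definitive treatment, there is no difference.

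**Step 2. Effect on time to union (illustration)**

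Assume a gap g between stages and the same total time T from first stage to union in both groups. The staged patient is recorded as T − g, so the share removed is g / T. Neither g nor T is given in the article.

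| g (days) | T = 180 days | T = 120 days |
|---|---|---|
| 7 | 7/180 = 3.9% | 7/120 = 5.8% |
| 14 | 14/180 = 7.8% | 14/120 = 11.7% |
| 42 | 42/180 = 23.3% | 42/120 = 35.0% |

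These apparent gains arise with no true difference in healing.

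**Step 3. Patients outside the follow-up population (illustration)**

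Inputs:
- N = 1000 (Sample size estimation).
- Staged share s = 15% to 30%, assumed. The lower end borrows the Background's statement that over 15% of tibia fractures are open, as a rough proxy only.
- Share f of staged patients who fail before definitive treatment = 1% to 10%, assumed.

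Excluded patients = N × s × f, from 1000 × 0.15 × 0.01 = 1.5 to 1000 × 0.30 × 0.10 = 30. That is 0.15% to 3.0% of the registry.

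**Step 4. Effect on a staged-group complication rate (illustration)**

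Take 25% in the patients retained, the lower end of the infection range that the Background quotes for complex open fractures. Suppose every excluded patient would count as an event, which is the extreme case, and that the denominator is the follow-up population. The rate with everyone counted is f + (1 − f) × 0.25:
- f = 1%: 0.01 + 0.99 × 0.25 = 25.75%
- f = 5%: 0.05 + 0.95 × 0.25 = 28.75%
- f = 10%: 0.10 + 0.90 × 0.25 = 32.5%

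On these inputs the staged group's rate is understated by 0.75 to 7.5 percentage points, although the loss to the whole registry is small.

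**The case against.** The best reply is that the definitions are explicit and mutually consistent, that counting from definitive fixation keeps times comparable with series that do the same, and that the aims are mainly descriptive and exploratory. Staged versus single-stage treatment is not named as a planned contrast, and the recorded staging data may let an analyst move the origin later. This stands in part: the definitive-treatment times are legitimate within a strategy and should be kept. It does not rescue their use across strategies, which is what stratification by treatment received and the stated main purpose call for. Nor does a change of origin bring back patients who were never followed.

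Several stronger readings are tempting, but the article does not support them:
- **The clock starts at consent.** Table 2's footnote b says "Informed consent may occur after treatment under certain circumstances" and bars data entry before consent, but no outcome is timed from consent. Late consent is a matter of delayed entry, and the surrogate consent described under Ethical considerations reduces it.
- **Infection between stages excludes a patient.** Nothing says so. A patient infected between stages who later has definitive treatment stays in.
- **This is immortal-time bias.** The inter-stage interval is left out, not credited to a group as event-free time. The correct description is unequal origins plus selection on reaching definitive treatment.
- **Early failures are certainly missing from complication rates.** The denominator is not tied to the follow-up population, enrolled patients who die or withdraw are analysed up to that time, and no origin is stated for infection and most other complications. The loss is possible, not established.
- **Day 0 in Table 2 is undefined for staged cases.** The article refers to visit-assignment rules and to a full protocol that are not shown, so this is not pressed.

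**Conclusion.** The point holds for comparisons by treatment strategy. As written, the plan drops the inter-stage interval from time to union and time to full weight bearing in staged patients, gives them a later one-year weight-bearing assessment, and leaves out of the follow-up population consented patients who never reach definitive treatment. The direction tends to favour staged treatment.

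The size cannot be derived from the article, which gives neither the gap between stages, nor the share of patients staged, nor the share failing before definitive treatment. The figures in the working only show that a negligible effect on the registry as a whole can be material within the staged group. Even the direction of the exclusion effect assumes that a patient who fails after a temporary first stage belongs with the staged strategy, and the article does not state how such patients are classified. Summaries that make no comparison between strategies are little affected.

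**What to change.** - **Population.** Define the follow-up population as consented, eligible patients from the first operative stage.
- **Complications.** Count complications from that stage, and tie the denominator to that population, including patients who never reach definitive treatment. Report their number and outcomes.
- **Time outcomes.** For any comparison across strategies, report time to union and time to full weight bearing from injury or from the first operative stage. Keep the times from definitive treatment as a within-strategy description.
- **Safeguard.** Classify patients by the strategy intended at the first stage, or treat conversion as time-varying, or use a landmark. Without this, the earlier origin would itself create immortal time: a patient grouped as staged by operations completed must have survived to the second one, and those who did not would be counted as single-stage.

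The cost is mainly a change of definitions and does not touch care. Staged patients' times will look longer and will be less comparable with series counted from definitive fixation. The dates of each stage must be available; the article lists the number of stages and the time from injury to index surgery but does not expressly list stage dates. Intended strategy is not expressly listed either and may need an added field; otherwise use the time-varying or landmark option.
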